# Maintenance of recovered dilated cardiomyopathy patients with half-dose neurohumoral blockades (MED-CHARM): A protocol for an open-label, pilot, randomized trial

**DOI:** 10.3389/fcvm.2022.966537

**Published:** 2022-08-12

**Keywords:** recovered dilated cardiomyopathy, neurohumoral blockades, heart failure, dosage adjustment, randomized controlled trail

## Abstract

**Methods:**

An open-label, randomized controlled, prospective study will be conducted among eligible patients with recDCM. During the pilot study phase, we will recruit 50 patients. The primary endpoint is hospitalization for heart failure or heart failure relapse within 12 months. Secondary endpoint is major adverse cardiovascular events, including cardiovascular mortality, myocardial infarction, stroke, sustained atrial tachycardia, or ventricular tachycardia. The results will be analyzed using intention-to-treatment analysis.

**Discussion:**

The study will provide important evidence of whether it is safe and effective to halve the dosage of neurohumoral blockades in recDCM patients.

**Trial registration number:**

ChiCTR2100054051 (www.chictr.org.cn)

## Background and rationale

Patients with dilated cardiomyopathy (DCM) have a poor prognosis, manifested by persistent left ventricular enlargement and progressive deterioration of systolic function, ultimately leading to heart transplantation or death (1). On the other hand, the disease burden of DCM is increasing globally, including in China. In 2015, the global burden of disease study estimated that the global number of cardiomyopathy is 2.5 million, a figure that increased by 27% from 10 years ago (2). A study in China in 2014 showed a mortality of 42.24% among 767 patients with DCM in 52 months (3). Furthermore, to the best of our knowledge, DCM often affects young patients with fewer comorbidities and a theoretically high life expectancy (4). Consequently, the exploration of the progress and outcome in patients with DCM is important to improve the prognosis and reduce societal burden.

DCM patients with heart failure have improved survival with the benefits of angiotensin-converting enzyme inhibitors (ACEI) or angiotensin receptor blockers (ARB), beta-blockers, and spironolactone (5). The complete normalization of left ventricular ejection fraction (LVEF) in some heart failure patients has been termed heart failure with recovered ejection fraction (HFrecEF) (6). Among patients with HFrecEF, DCM occupies a high proportion, just second to heart failure resulting from energy and metabolic disorders (e.g., thyroid disease-related cardiomyopathy) (6). Due to the lack of a standardized definition and the current data from observational studies and clinical trials, the proportion of patients with improved ejection fraction ranges from 10% to 40% (6). In some of the patients with DCM, the ejection fraction and cardiac chamber size was observed to completely return to normal, which has been termed recovered dilated cardiomyopathy (recDCM) in some studies (7). However, there is a lack of relevant evidence to support the clinical management of patients with recDCM, thereby, the recommendations in guidelines remains sparse.

The fact that there has only been one prior prospective, randomized, controlled study in patients with recDCM is a mixed blessing. The TRED-HF study, withdrawal of pharmacological treatment for heart failure in patients with recovered dilated cardiomyopathy, published in *Lancet* in 2018, explored the safety and efficacy of withdrawing all drugs in patients with recDCM. That study found a significantly higher proportion of heart failure recurrence in the withdrawn group, while in the control group, there was no relapse at half-year follow-up, indicating that such patients were not suitable for total withdrawal treatment (7). However, all the patients in the control group took the guideline-recommended dosage, and it is not clear whether the cardiac function could be maintained normal if the drug class is not changed while the dose is halved.

In addition, many previous studies point out that in the actual clinical practice, many heart failure patients often fail to reach the target doses of guideline-directed medical therapy (GDMT) because of complicated multiple comorbidities (8–12), which is a great challenge to successfully up-titrate classes of HF medications (13). Moreover, a previous study showed that the best outcomes among heart failure patients were observed in those with a combination of ACEI/ARB and beta-blockers therapy, and unfortunately, this was rarely reached. Patients with the combination therapy of the two drugs reaching more than half of the target dose have better prognosis than those with a single drug therapy titrating to the target dose (14). Accordingly, we assume that the above speculation may apply to the clinical practice of recDCM.

Insights into the pathophysiological mechanisms of heart failure in recovered DCM patients, as well as advances in drugs for heart failure, have enabled the possibility of drug reduction in such patients. First, factors promoting adverse cardiac remodeling in patients with heart failure with recovered ejection fraction have been already suppressed with guideline-directed medications, and one study suggests that there may be a strong attenuation of adverse remodeling factors, such as sympathetic activation and renin angiotensin aldosterone system (RAAS) activation (6). In such circumstance, it may be possible for recDCM patients to reduce the doses of medications for heart failure. Second, with the advent of angiotensin receptor-neprilysin inhibitor (ARNI) and sodium-glucose cotransporter 2 inhibitors (SGLT2-i), patients have experienced significant improvement in the treatment of heart failure compared with previous ones (15). As a consequence, with the application of current novel class of drugs inhibiting cardiac remodeling, the original “ACEI/ARB/ARNI + beta-blockers” doses may have room for diminution. Actually, there are instances in which cardiac function is normalized in a subset of patients with low doses of GDMT for heart failure (14). These indicate that there may be a subset of patients who do not require a target dose to maintain cardiac function, and lower doses may be adequate. Thus, we reasoned that the “ACEI/ARB/ARNI + beta-blockers” halving dose therapy may be non-inferior to original target dose in maintaining cardiac function in recDCM patients.

This is an open-label, randomized controlled, prospective study that will be conducted in patients with recDCM, comparing the safety and efficacy of original target dose and halved dose of “ACEI/ARB/ARNI + beta-blockers.” This will provide essential evidence of whether it is safe and effective to reduce doses of neurohumoral blockades in recDCM patients.

## Methods and analysis

This is an open-label, randomized controlled, prospective study. Following the guidance of the ethical committee at our institution, we will recruit 50 patients in the pilot study phase.

### Patients' recruitment

All patients with recDCM referred to Xinqiao Hospital (Army Medical University, Chongqing, China) will be screened by a senior cardiologist. Patients and their guardians are required to sign written informed consent. A special staff member will carefully describe the study to the patients and their guardians.

### Inclusion criteria

Age≥18 years old.Previous diagnosis of dilated cardiomyopathy with LVEF <40%.Current therapeutic drugs with at least one of ACEI/ARB/ARNI and beta-blockers. Both ACEI/ARB/ARNI and beta-blockers doses are not up-titrated within 6 months; Other GDMT include a mineralocorticoid receptor antagonist (MRA), a SGLT2-i or diuretics.Without symptoms of heart failure, and no hospitalization for heart failure for more than 6 months.With at least two independent echocardiography (with interval ≥6 months) show that LVEF ≥50%, and left ventricular end-diastolic volume index (LVEDVi) <97ml/m^2^.With written informed consent.

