### Sample size

Regarding the results from clinical trials in heart failure patients, the incidence of cardiac death or heart failure readmission within 12 months is 15–30% with guideline-directed medical therapy. The patients with DCM enrolled in this study have recovered cardiac function and ejection fraction, and TRED-HF study showed a primary endpoint event rate of 0% in such patients with medication doses unchanged in 6 months. Thus, in this study, it is estimated that the primary endpoint rate in control group and in withdraw group is 5 and 7% over 12 months of follow-up. It is estimated that 218 patients would provide the trial with 80% power to show the non-inferiority of halved doses to original doses, a two-sided alpha of 0.05 and a non-inferiority margin of 10% is applied. Considering a loss to follow up rate of 10%, the final sample size is 240. According to the suggestion of the ethical committee, the current study is a pilot study and 50 patients are intended to be included initially, 25 patients per group. After the initial analysis, more patients might be recruited in a further stage of the study.

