**Figure 1 F1:**
[figure not shown]
Study flow diagram.

In the withdraw group, the doses of ACEI/ARB/ARNI will be reduced by 50% firstly. The symptoms and signs will be assessed in the following 1 month. The echocardiography and NT-proBNP will be performed to see if they could tolerate a further dose reduction of beta-blockers. Then, the dose of beta-blockers will also be reduced by 50% if the cardiac function of participants is stable. The other drugs of the participants will keep unchanged during the follow-up. In the control group, ACEI/ARB/ARNI, beta-blockers, spironolactone, SGLT2-i, and other drugs will be taken with original doses during the follow up.

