## Discussion

The main aim of the present study is to evaluate the efficacy and safety of patients with recDCM who received half-dose neurohumoral blockades and received original dose maintenance therapy, and then by comparing the two doses of treatment, it may be concluded that “ACEI/ARB/ARNI + beta-blockers” halving dose was non-inferior to patients' maintenance dose in maintaining recovered cardiac function in DCM patients. This will provide a significant basis for the choice of whether to reduce dosage or to adhere to original dose maintenance therapy in DCM patients who recovered, to reduce the economic and psychological burden on patients.

Furthermore, this study is only the pilot study of the original research we want to do because the ethics committee needs to protect the interests of patients. Therefore, one of the limitations of this study is the small sample size, and if this study is effective, we will conduct more research.

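### The dose-stability criterion bars only recent increases, so a patient whose dose was recently lowered can be enrolled without recovery having been confirmed on that dose

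*Protocol article*

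**What the plan says.** All references are to the protocol article.

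- **Inclusion criteria, dose:** "Both ACEI/ARB/ARNI and beta-blockers doses are not up-titrated within 6 months". No minimum dose is set, and reductions are not mentioned.
- **Inclusion criteria, clinical state:** "Without symptoms of heart failure, and no hospitalization for heart failure for more than 6 months".
- **Inclusion criteria, imaging:** "With at least two independent echocardiography", at least 6 months apart, must show recovered LVEF and LVEDVi. The criterion does not link either scan to the dose being taken at entry.
- **Exclusion criteria:** none of the eight items concerns a recent dose change.
- **Intervention, withdraw group:** "the doses of ACEI/ARB/ARNI will be reduced by 50% firstly". Symptoms and signs are assessed over the following month, and echocardiography and NT-proBNP are done "to see if they could tolerate a further dose reduction of beta-blockers".
- **Intervention, control group:** these patients' neurohumoral blockers and "other drugs will be taken with original doses during the follow up".
- **Purpose:** the Sample size section aims "to show the non-inferiority of halved doses to original doses". The Discussion describes the comparator as patients who "received original dose maintenance therapy".

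**The concern.** The trial asks whether a patient who has recovered on a maintenance dose can hold that recovery on half of it. That needs a starting dose on which recovery has been seen to last. A rule against recent increases secures this from one side only. If the dose was lowered two months before screening and both echocardiograms predate the change, the patient meets every stated criterion, yet recovery has not been documented on the current dose.

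Three things follow:

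1. **Safety.** In the withdraw group, a second reduction can follow closely on the first, with no imaging evidence that the first was tolerated.
2. **Meaning of the comparator.** A recently reduced control is not on an established maintenance dose. The Sample size section supports its low control-group rate with an earlier trial in which patients on unchanged doses had no events over 6 months.
3. **Attribution.** A relapse set off by the pre-trial reduction would be counted as a primary endpoint event in whichever arm the patient was assigned to.

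**Working it through.** **Step 1. Can such a patient enter?** Take a patient who meets the other criteria and whose ACEI/ARB/ARNI and beta-blocker doses were lowered within the last 6 months.

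| Requirement | Met? | Reason |
|---|---|---|
| No up-titration within 6 months | Yes | The change was downward |
| No symptoms; no heart failure hospitalization for more than 6 months | Yes, if clinically quiet | Concerns clinical state, not dose |
| Two recovered echocardiograms at least 6 months apart | Yes | Both may predate the reduction |
| Eight exclusions | Not triggered | None concerns dose change |

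The patient is eligible as the rule is written.

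**Step 2. What happens after randomization?** Under Intervention, a control continues the current dose. A withdraw-group patient has the ACEI/ARB/ARNI dose cut first, and the echocardiography and NT-proBNP check follows. That check protects against the beta-blocker cut but not the first one. The baseline list under Follow-up and measurement includes examination, laboratory tests, NYHA class, walking test and KCCQ, but names no echocardiogram.

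**Step 3. How large could the effect be?** The plan gives no figure on this point, so there is none to reproduce. Everything below is illustrative. Let f be the share of patients reduced before entry (assumed 1–30%), and take the earlier cut as a halving of both drugs.

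*Dose, as a percentage of the dose on which recovery was shown:*
- control: 100(1 − f) + 50f
- half-dose arm: 50(1 − f) + 25f
- contrast: 50 − 25f

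If the earlier cut was smaller, to a fraction k of the previous dose, the contrast is 50 − 50(1 − k)f. With k = 0.75 and f = 10% it is 50 − 1.25 = 48.75, against 47.5 for a halving.

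*Event-rate difference at the planning margin.* Assume 5% at full dose, 15% at half dose and r at quarter dose.
- control: 5(1 − f) + 15f
- half-dose arm: 15(1 − f) + rf
- difference: d = 10 − f(25 − r) percentage points

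*Event-rate difference at the plan's own rates* (5% and 7%, Sample size). Here d = 2 + f(r − 9), with r taken as 7% to 11%.

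| f | Dose contrast | d at 5%/15%, r = 15% / 25% / 35% | d at 5%/7%, r = 7% / 9% / 11% |
|---|---|---|---|
| 0 | 50 | 10 / 10 / 10 | 2 / 2 / 2 |
| 1% | 49.75 | 9.9 / 10 / 10.1 | 1.98 / 2 / 2.02 |
| 5% | 48.75 | 9.5 / 10 / 10.5 | 1.9 / 2 / 2.1 |
| 10% | 47.5 | 9 / 10 / 11 | 1.8 / 2 / 2.2 |
| 20% | 45.0 | 8 / 10 / 12 | 1.6 / 2 / 2.4 |
| 30% | 42.5 | 7 / 10 / 13 | 1.4 / 2 / 2.6 |

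The shift is zero when each halving adds the same risk. It is toward non-inferiority when the second halving adds less than the first, and against it when the second adds more.

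**Step 4. Against the precision of the pilot.** With 25 per arm and rates of 5% and 7%, the standard error of the difference is √(0.05 × 0.95/25 + 0.07 × 0.93/25) = √(0.0019 + 0.002604) = 0.067, or 6.7 points. Expected control events are 25 × 0.05 = 1.25, and one event is 1/25 = 4 points. An average shift of 0.1–0.5 points (f of 1–5%) is small beside this. A single relapse due to an earlier reduction would still be visible in the pilot result.

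**The case against.** The strongest reply is that the contrast actually randomized is intact. Each patient either halves the current dose or continues it, and no minimum dose is required, so a previously reduced patient receives exactly that contrast. This stands. The fall in contrast from 50 toward 42.5 points appears only when doses are expressed relative to the dose on which recovery was shown, a scale the protocol does not use.

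A reader might infer that reduced-dose controls dilute the difference and so favour a non-inferiority finding. The documents do not support this. The same kind of patient in the withdraw group goes lower still, and the net effect depends on how risk changes from half to quarter dose, which the article does not say. A reader might also suppose that patients would literally be halved twice. That holds only if the earlier change was itself a halving of the drugs concerned. A smaller step gives smaller figures.

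There are safeguards: screening by a senior cardiologist, the symptom and hospitalization criteria, staged reduction, and visits at 1, 3, 6 and 12 months. They lower the risk but do not stop a recently reduced patient from entering, and the imaging check comes after the first cut.

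It can also be said that scan timing and a definition of the original dose belong in a full protocol, and that admitting patients reduced for tolerability is pragmatic. The first argument is fair as to detail, but the one-directional criterion is stated explicitly and is not an omission of detail. The second would defend enrolling patients on low doses, which the proposed wording still allows once the dose has been stable.

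**Conclusion.** The point holds as a gap in an explicitly stated criterion. As written, the rule admits patients whose recovery was never confirmed on the dose that the trial will continue or cut. The consequences are avoidable patient risk, a blurred reading of half versus maintenance dose, and possible counting of relapses that a pre-trial reduction caused.

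It does not bias the randomized comparison of halving with continuing the current dose, and it has no fixed direction for non-inferiority. The affected share is not given and is probably small. The event-rate shifts above rest on an assumed share, an assumed earlier halving of both drugs and assumed quarter-dose risk (and, at the margin, an assumed 15% half-dose risk), so no error rate can be attached. The change is worth making because it is cheap and bears on safety, not because a large distortion has been shown.

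**What to change.** In the Inclusion criteria, replace the bar on up-titration with a requirement that ACEI/ARB/ARNI and beta-blocker doses be *unchanged, neither raised nor lowered, for at least 6 months before randomization*, and that the latest qualifying echocardiogram be done on that dose. Under Intervention, define the original dose as that stable dose.

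The cost is a few words in one criterion and one definition. Recently reduced patients wait until they have 6 months on a stable dose, which slows recruitment slightly. Patients stable on a low dose remain eligible, and the sample-size inputs do not change. The same wording can serve any further stage of recruitment after the pilot.

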### Exclusion criteria

One of the following conditions is met:

1. Uncontrolled hypertension (blood pressure≥160/100 mmHg).2. Valvular heart disease with moderate or greater severity.3. Severe renal insufficiency (estimated glomerular filtration rate (eGFR) <30 ml/min/1.73 m^2^, estimated according to Cockcroft-Gault formula).4. Atrial, supra-ventricular, or ventricular arrhythmia requiring beta-blockers.5. With the implantation of intra-cardiac defibrillator or cardiac resynchronization therapy.6. Ischemic heart disease.7. With severe systemic diseases.8. Diagnosed with secondary cardiomyopathies.

### Randomization

The enrolled patients will be randomly assigned into two groups. The randomization list will be automatically generated by the computer system. Before the start of the trial, the randomization list will be configured into the interactive network response system (IWRS, Jinling Rat mini-apps, Nanjing Jihu Network Technology Co., Ltd, Jiangsu, China), and IWRS will assign random numbers to these finally screened patients. Finally, the patients will be randomly assigned to either the withdraw group or control group with a ratio of 1:1 using IWRS.

### Primary endpoint

The patients will be followed up for 12 months. The primary endpoint is hospitalization for heart failure or heart failure relapse. Heart failure relapse is defined if one of the following criteria is met: (1) LVEF reduction≥10% with LVEF <50%; (2) LVEDVi increased by more than 10%, and exceeded the normal values; (3) 2-fold elevation of NT-proBNP and more than 400 pg/ml; (4) Clinical evidence of heart failure (judged by symptoms, signs and supplementary examination).

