### Statistical analysis

Studies will be analyzed using intention-to-treatment and included all patients randomized, regardless of treatment received. Continuous data are expressed as mean ± SD or interquartile range (IQR 25–75). Categorical variables are expressed as a percentage. Continuous variables are compared by an independent sample *t*-test or rank-sum test. The chi-square or Fisher's exact test is used in the analysis of categorical variables. The Cox proportional hazards model was used to analyze and compare the differences in the occurrence of primary endpoint events and key secondary endpoint events within 12 months of follow-up between the trial group and the control group, and the hazard ratio (HR) and 95 % confidence interval will be calculated.

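### In an open-label trial, a judged relapse criterion with no required finding is enough alone for a primary event, and no masked assessment is described

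*Protocol article*

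**What the plan says.** Methods and analysis gives the design: "This is an open-label, randomized controlled, prospective study". Under Primary endpoint, "The primary endpoint is hospitalization for heart failure or heart failure relapse", with 12 months of follow-up. The rule for relapse is "Heart failure relapse is defined if one of the following criteria is met".

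- Criterion 1 is a fall in LVEF of at least 10% to a value under 50%.
- Criterion 2 is "2) LVEDVi increased by more than 10%, and exceeded the normal values".
- Criterion 3 is "3) 2-fold elevation of NT-proBNP and more than 400 pg/ml".
- Criterion 4 is "Clinical evidence of heart failure (judged by symptoms, signs and supplementary examination". It names no sign, test or result that must be present, and no assessor. It need not coincide with criteria 1 to 3.

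The Intervention section describes a two-step reduction in the withdraw group. The ACEI/ARB/ARNI is halved first. After a month of clinical observation, echocardiography and NT-proBNP inform whether the beta-blocker is halved too. The control group keeps its doses, so it has no such decision.

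Under Statistical analysis, "The Cox proportional hazards model was used to analyze and compare the differences in the occurrence of primary endpoint events", with all randomised patients included and a hazard ratio with 95% confidence interval reported. The article mentions neither masked echo reading nor independent adjudication of events.

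**The concern.** Randomisation and intention-to-treat analysis protect against imbalance and selective exclusion. They do not protect against events being called differently in the two arms. Patients know whether their dose was halved, and their symptoms feed criterion 4. Staff who know the dose group may look harder for deterioration in the halved-dose arm, or may discount equivocal signs there because they expect the reduction to be safe.

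The two directions have different consequences for a non-inferiority aim. Over-calling in the reduced-dose arm is conservative: it makes non-inferiority harder to show. Under-calling in that arm moves the estimate towards no difference and can support a claim that halving is acceptable when it is not. With few events expected, a handful of judged calls matters in either direction.

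**Working it through.** **Is the allocation known to those who judge?** Three sections read together:

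1. Methods and analysis: treatment is open-label.
2. Intervention: the second dose step is decided in one arm only, so whoever decides it knows the arm. The decision uses symptoms, signs, echo and NT-proBNP.
3. Primary endpoint: the same kinds of information define relapse.

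The treating team therefore knows the allocation while handling the data that define relapse. Nothing in the article separates that team from endpoint assessment, although no endpoint assessor is named.

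**Inputs for size** (Sample size section): 12-month event rates of 5% (control) and 7% (reduced dose), margin 10%, read here as absolute percentage points, 80% power, 218 evaluable patients, 1:1 allocation.

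**Reproducing 218.** For two proportions with unpooled variance,

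n per arm = [pC(1−pC) + pT(1−pT)] × (z_α + z_β)² / [margin − (pT − pC)]²

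= (0.0475 + 0.0651) × (1.645 + 0.842)² / (0.10 − 0.02)² ≈ 108.8, so 109 per arm and 218 in total.

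This uses a one-sided 0.05. A two-sided 0.05 (one-sided 0.025) gives 139 per arm, 278 in total. The mismatch with the stated two-sided level is a separate matter; both levels are shown below.

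**Expected events at 109 per arm:** 109 × 0.05 = 5.45 and 109 × 0.07 = 7.63.

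**Effect of two discretionary calls in one arm:** 2/109 = 1.8 percentage points. The assumed true difference is 7 − 5 = 2 points, and 1.8/10 = 18% of the margin.

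**Effect on operating characteristics.** The article gives no rate for criterion 4, so the shifts are assumptions. On the risk scale used for the sample size, with pT now the rate as called,

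P(non-inferiority) = Φ{[margin − (pT − pC)] / SE − z_α}, where SE = √{[pC(1−pC) + pT(1−pT)] / 109}.

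- Over-calling by 2 points (5% v 9%): SE = √(0.1294/109) = 0.0345; 0.06/0.0345 − 1.645 ≈ 0.10; power 53.8%.
- Under-calling by 2 points when the true rates lie at the margin (5% v 15%, called as 5% v 13%): SE = √(0.1606/109) = 0.0384; 0.02/0.0384 − 1.645 ≈ −1.12; false non-inferiority 13.1%.

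| Shift in the reduced-dose arm | One-sided 0.05 | One-sided 0.025 |
|---|---|---|
| Power, no shift | 80.1% | 70.2% |
| Power, +1 point | 67.6% | 55.6% |
| Power, +2 points | 53.8% | 41.3% |
| False non-inferiority, no shift | 5.0% | 2.5% |
| False non-inferiority, −1 point | 8.2% | 4.4% |
| False non-inferiority, −2 points | 13.1% | 7.5% |

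These are normal approximations for a risk difference. The planned analysis is a Cox model, so they indicate size and do not predict its result.

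**The case against.** The strongest reply is that a clinical criterion is a sensible choice in a dose-reduction trial with a safety aim, because it catches deterioration that the numeric thresholds miss. That stands: criterion 4 should remain in the composite.

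A reader might also infer more than the documents support:

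- **That criterion 4 is purely clinical.** It includes supplementary examination. The fair criticism is that no examination or result is required.
- **That no objective-only analysis is planned.** The article shows none, but component analyses are commonly left to a full protocol or SAP, and neither is at hand. Its absence is not a defect; the supportive analysis is proposed as a remedy.
- **That event assessors are known to be unmasked.** No assessor is named, and masked echo reading is compatible with open-label treatment. What the text does show is that the treating team knows the allocation.
- **That a knowing echo reader can easily create an event.** Criteria 1 and 2 each need two conditions, so moving one reading across one threshold is enough only if the other condition also holds.
- **That one component decides the result, or that the bias is as large as the margin.** With no criterion-4 rate, and no information on how often such patients also meet criteria 1 to 3 or are admitted, neither follows. A shift of 1.8 points is under a fifth of the margin.
- **That one call worth 1/25 = 4 points in the pilot measures the bias.** Any event, including one defined by the laboratory, moves an arm of 25 by 4 points. That reflects the pilot's size, which the Discussion acknowledges.

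**Conclusion.** The point holds in a limited form. A judged criterion with no required finding is enough alone for a primary event in an open-label trial, and no masked assessment of it or of the echo readings is described. The comparison is therefore open to differential calling in either direction, and under-calling in the reduced-dose arm is what threatens a false non-inferiority conclusion.

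At 109 per arm, two calls amount to 1.8 points, nearly the whole assumed 2-point difference but well short of the 10-point margin. This rests on the plan's 5% and 7% rates, a margin read as absolute, and assumed shifts. The documents show that such bias is possible and not guarded against in the text; they do not show that it will occur or how large it would be. The remedies are cheap enough to be worth making on that basis.

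**What to change.** (a) Have the hospital's existing echo staff report LVEF and LVEDVi in both arms without dose-group information on the request. The treating team still receives the report. NT-proBNP is a laboratory value and needs no change. The cost is a change to the request form.

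(b) Prespecify a supportive analysis that repeats the primary comparison, with the Cox model already named, counting criteria 1 to 3 and heart failure hospitalisation and leaving out events that rest on criterion 4 alone. Report it beside the full composite. This requires recording, for each event, which criteria were met and when. State that hospitalisation is itself partly discretionary, so this version is less dependent on judgement but not free of it. Do not make it an additional gate for the non-inferiority claim; its role is to show whether the result leans on criterion 4.

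Neither step needs a new reader or a committee, changes treatment, or alters the primary endpoint. The downside is fewer events and a wider interval in the supportive analysis, which will be especially imprecise in the pilot, where only 25 × 0.05 = 1.25 and 25 × 0.07 = 1.75 events are expected under the full composite.
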